#### General analysis principle

Normality will be examined using the Shapiro-Wilk test. For normal distribution, continuous variables will be described as mean and standard deviation (SD) and compared using the *t*-test. For non-normal distribution, continuous variables will be described as medians and interquartile range (IQR) and compared using the Mann-Whitney test. test. Categorical variables will be expressed as frequencies and percentages and compared using chi-squared test or Fisher exact test when appropriate. We have no imputation plans for missing data. All statistical tests will be tested with two sides, *P* < 0.05 is considered to represent a statistically significant difference, with a CI of 95%. All analyses were performed using Stata (Stata Corporation, version 15, College Station, TX, USA).

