### Randomization

After enrollment, randomization and allocation will be done on the day of surgery. The randomization will be centralized in the Guancui EDC system. We applied a randomized block design with a block number of six in a 1:1 ratio. A data manager who is independent of the data analysis or patient enrolment will generate the randomization schedule at the beginning of this trial. After providing informed consent, patients who are consistent with the inclusion and exclusion criteria will be randomly assigned to the treatment group or the control group. The randomization schedule will not be available to study recruiters or physicians. The allocation is only available for the independent data manager and the specific study coordinators in the Guancui EDC system. Specifically, when appropriate patients are enrolled, the researcher will inform the data manager, and then the random number and exact treatment group will be returned simultaneously.

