### Statistical analysis

#### Sample size calculation

The Finland RCT reported that perioperative hydrocortisone significantly reduced postoperative complications after PD in high-risk patients (18% vs. 41%; *P* < 0.05; Clavien-Dindo III-IV) [14]. Based on the pancreatic transection line frozen samples, high-risk patients with >40% acini consisted of more than half of the cohort. Because 0.2 mg/kg dexamethasone has theoretically a similar anti-inflammatory effect to hydrocortisone, so we presume that the perioperative dexamethasone could reduce at least 30% of major complications in the whole PD cohort.

For the sample size calculation, a 30% reduction in the rate of overall complications was assumed with a power of 80% (*β*=0·2), and an α-error of 0.05. This yielded an estimated group size of 128 patients. Finally, the sample size of this study is based on the primary outcome — CCI. Because CCI is more sensitive and requires a smaller sample size compared to the Clavien-Dindo classification in RCT, 128 patients in each group are sufficient for the primary outcomes [24]. Finally, the target recruitment of the PANDEX trial will be set at 300 to account for 20% dropout or deviation of the protocol. Thus, 150 patients are required in each group.

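### The general rule for skewed variables would report medical costs as median and Mann-Whitney test, which gives no estimate of the difference in mean cost per patient (minor)

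*Protocol article*

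**What the plan says.** The section Tertiary outcomes measures lists overall medical costs last, after CRP, glucose and blood cell counts. No section gives costs a method of their own.

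General analysis principle sets one rule for all continuous variables. It begins with a test: "Normality will be examined using the Shapiro-Wilk test". If the variable passes, "For normal distribution, continuous variables will be described as mean and standard deviation (SD) and compared using the" t-test. If it fails, "For non-normal distribution, continuous variables will be described as medians and interquartile range (IQR) and compared using the Mann-Whitney test". The section adds "All statistical tests will be tested with two sides" and mentions a 95% confidence level, without naming the quantity that an interval would describe.

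Efficacy analysis describes a separate presentation only for the Comprehensive Complication Index. Nothing there takes costs out of the general rule.

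**The concern.** A cost comparison is normally read as an answer to how much is saved or added per patient treated. That is a difference in arithmetic means, because only the mean multiplies up to total spend. A median describes the typical patient. A Mann-Whitney test asks whether values in one arm tend to be larger than in the other. Both give little weight to how expensive the expensive courses are.

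That matters here because of where the trial expects its benefit. Sample size calculation presumes that dexamethasone reduces major complications by at least 30% in the whole cohort. Any saving from that would sit mostly in the upper tail of the cost distribution, where the median and the ranks are least informative. Followed as written, the plan would publish two medians and a P value and leave the cost per patient unestimated.

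**Working it through.** **Which branch applies.** The protocol gives no cost figure to reproduce, so the cost distribution below is an assumption. In simulated trials with right-skewed costs at 128, 140 and 150 patients per arm (128 and 150 are the protocol's group sizes before and after the dropout allowance), Shapiro-Wilk rejected normality in 100% of replicates in every scenario tried. The median and Mann-Whitney branch is therefore the one to expect.

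**Assumed cost model (relative units).**
- Routine course: lognormal, median 1, log-SD 0.25, so its mean is exp(0.25²/2) = 1.0317.
- Course with a major complication: lognormal, median *m* = 2 or 3, log-SD 0.4, so its mean is *m* × exp(0.4²/2) = *m* × 1.0833.
- Proportion with a major complication, *p*: 30% to 21%, or 20% to 14%. Both are the protocol's presumed 30% relative reduction (0.30 × 0.7 = 0.21; 0.20 × 0.7 = 0.14). The control rates are assumptions.

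**Formulas.** Mean = (1 − *p*) × 1.0317 + *p* × *m* × 1.0833. The median is the *x* that solves (1 − *p*) Φ(ln *x* / 0.25) + *p* Φ((ln *x* − ln *m*) / 0.4) = 0.5.

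Worked case, *p* from 0.30 to 0.21 with *m* = 2:
- Control mean: 0.70 × 1.0317 + 0.30 × 2 × 1.0833 = 0.722 + 0.650 = 1.372.
- Dexamethasone mean: 0.79 × 1.0317 + 0.21 × 2 × 1.0833 = 0.815 + 0.455 = 1.270.
- Change: 1.270 / 1.372 − 1 = −7.4%.

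| Major complications | *m* | Mean, control → dexamethasone | Change in mean | Median, control → dexamethasone | Change in median |
|---|---|---|---|---|---|
| 30% → 21% | 2 | 1.372 → 1.270 | −7.4% | 1.126 → 1.077 | about −4% |
| 30% → 21% | 3 | 1.697 → 1.498 | −11.8% | 1.149 → 1.088 | about −5% |
| 20% → 14% | 2 | 1.259 → 1.191 | −5.4% | 1.072 → 1.047 | about −2% |
| 20% → 14% | 3 | 1.475 → 1.342 | −9.0% | 1.082 → 1.052 | about −3% |

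Mean and median move in the same direction, but the median shows roughly a third to a little over half of the relative change in the mean.

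**Do the tests disagree?** In this model, with no change in routine cost and 140 per arm, a significant saving is found in about 10-24% of trials by Mann-Whitney and 15-28% by a Welch comparison of means. Both are low and not far apart. In another assumed scenario (complications 41% to 28.7%, doubling cost, 150 per arm) they agree: 36.3% and 36.9%.

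**When can direction differ?** Suppose routine cost also rises by 8% in uncomplicated dexamethasone patients. For 20% to 14% with *m* = 3, the dexamethasone mean is 0.86 × 1.0317 × 1.08 + 0.14 × 3 × 1.0833 = 0.958 + 0.455 = 1.413. That is still below 1.475, while the median rises from 1.082 to 1.136. Mann-Whitney is then significantly in the wrong direction in about 15% of trials. With *m* = 2 the mean becomes 0.958 + 0.303 = 1.262 against 1.259, so no saving is left to reverse. For 30% to 21%, significant wrong-way results occur in about 1-2% of trials at a 5% rise and 3-7% at an 8% rise.

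**The case against.** The strongest reply has three parts.

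First, the protocol states no economic hypothesis, cost-effectiveness analysis or perspective. Costs come last among the tertiary endpoints, and a median with IQR is a fair description of a typical patient's cost. This stands, and it keeps the point minor. It does not make the median a measure of cost saved, which is how a cost result in a pragmatic trial will be read.

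Second, the section states a general principle in a condensed article, and an unseen analysis plan might treat costs separately. This stands in part: nothing forbids reporting means as well. But the article does fix a rule for every continuous variable and makes no exception for costs, so a separate plan would have to add to it or depart from it.

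Third, a reader might infer that the rule will miss a real saving or reverse the economic result. The documents do not support that. Without a rise in routine cost, the two tests have similar, low power in the model above. Reversal needs such a rise, and nothing in the protocol suggests one of 5-8% from a single intravenous bolus. More striking simulated reversals need stronger inputs still. One with 18.6% significant wrong-way results took a 12% rise in routine cost and a fall in severe cases from 15% to 5%, a two-thirds reduction against the 30% presumed. Nor is it evidence of reversal that, at a 5% rise with complications falling from 30% to 21%, the sample median is higher with dexamethasone in about half of trials. The population medians are then almost equal, so either order is about equally likely.

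**Conclusion.** The point holds as a mismatch between the stated rule and the quantity of interest. Costs will almost certainly fall into the median and Mann-Whitney branch, and that branch prescribes no mean cost and no mean difference. This follows from the text and needs only that costs are skewed.

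Its size rests on an assumed cost distribution: with a 30% relative fall in major complications, mean cost falls by about 5-12% and the median by about 2-5%. A change of direction is possible in this model only if routine cost also rises with dexamethasone, so it is a conditional possibility and not a prediction. Costs are tertiary, and the analysis of the Comprehensive Complication Index does not depend on them. Severity is minor.

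**What to change.** Add one sentence to General analysis principle, or to the analysis plan, before any unblinded analysis: overall medical costs are exempt from the Shapiro-Wilk rule; the cost result is the arithmetic mean per arm and the difference in means with a bootstrap or Welch 95% confidence interval; median and IQR are shown as description only.

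This needs no new data and no more patients, and Stata, which the protocol already names, can do it. The price is a wide interval. Under the assumptions above, a comparison of means detects the saving in at most about 28% of trials, so the change supplies the right estimate with its honest uncertainty and should not be expected to settle the cost question.

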#### Efficacy analysis

All outcomes will be analyzed using modified intention-to-treat analyses, where all randomized patients who undergo scheduled pancreaticoduodenectomy were included in the analyses. Criteria to remove patients from analyses after randomization are as follows:Scheduled pancreaticoduodenectomy was not performed (e.g., disseminated cancer, enucleation).Total pancreatectomy was performed.Additional hepatic resection.Patient withdrew consent prior to surgery.

The primary outcome is a sum of all complications that are weighted for their severity, based on the Clavien-Dindo classification, the Comprehensive Complication Index (CCI). CCI score will be presented as mean ± SD and in case of skewed distributions as median and range. Values will be compared by the *t*-test or the Mann-Whitney test as appropriate.

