## Methods/design

### Study design

The PANDEX trial is an investigator-initiated, multicentric, prospective, randomized, double-blinded, placebo-control, pragmatic study. The trial will be conducted in seven high-volume centers in China (>50 PDs per year). This study hypothesizes that the intraoperative use of dexamethasone can reduce the incidence of postoperative complications after PD. The flowchart of this study is shown in Fig. 1. This article adheres to the Standard Protocol Items: Recommendations for Interventional Trials (SPIRIT) statement [21, 22].

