### Primary outcome measures

The primary endpoint is the Comprehensive Complication Index (CCI) score within 30 days after the operation. The CCI takes into account all cumulative complications and receives values between 0 and 100 (Table 1) [24]. The CCI’s weight of complication (wC) is based on the established Clavien-Dindo classification [25]. Detail calculation was presented below.

**Table 1 Tab1:** The comprehensive complication index calculation

**Grade**	**wC**	**CCI single value**
Grade I	300	8.7
Grade II	1750	20.9
Grade III		
Grade IIIa	2750	26.2
Grade IIIb	4550	33.7
Grade IV		
Grade IVa	7200	42.4
Grade IVb	8550	46.2

Clavien-Dindo grade V always results in CCI 100

$$CCI=\sqrt{wC1+wC2\dots +wCx}/2$$; the online CCI calculator is available at www.assessurgery.com

*wC*, weight of complication; *CCI*, the Comprehensive Complication Index

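### The primary CCI analysis will in effect be an unadjusted Mann-Whitney test with no specified between-arm effect estimate, and centre and preoperative factors go unused

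*Protocol article*

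**What the plan says.** The endpoint is set under Primary outcome measures: "The primary endpoint is the Comprehensive Complication Index (CCI) score within 30 days after the operation". Under Efficacy analysis the comparison is fixed as "Values will be compared by the *t*-test or the Mann-Whitney test as appropriate", with this summary rule: "CCI score will be presented as mean ± SD and in case of skewed distributions as median and range". General analysis principle supplies the rule for choosing the test: "Normality will be examined using the Shapiro-Wilk test". That section gives median with interquartile range, not range, for non-normal variables. It also mentions a 95% confidence interval without saying of what quantity.

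Under Study design, "The trial will be conducted in seven high-volume centers in China". Randomization describes 1:1 allocation in blocks of six and states no stratification. Surgical approach, diagnosis, pancreatic texture and preoperative diabetes appear only under Subgroup analysis, as examples for exploratory post-hoc work. No centre term, covariate or model is named for the primary comparison.

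**The concern.** Three features of the stated analysis look weak.

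- **The choice of test is left to the data, although its outcome can be foreseen.** The t-test concerns a difference in means and Mann-Whitney a comparison of ranks. The shape of CCI practically settles which one is used, so the pre-test does no work.
- **The expected branch carries no stated effect measure.** A p-value beside two medians does not tell a reader how much dexamethasone helps. On a stepped scale the two medians can also be equal when there is a real benefit.
- **Centre and preoperative risk are left out.** If they predict CCI, an unadjusted comparison is less precise than it could be at the same sample size.

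At stake are how interpretable the primary result is and a modest amount of precision. The validity of the test is not in question.

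**Working it through.** **1. The plan's own figure.** The sample size section says "a 30% reduction in the rate of overall complications was assumed with a power of 80" per cent, with "an α-error of 0.05", and arrives at 128 per group. This is a calculation for two proportions, and no control rate is given, so it cannot be reproduced directly. The formula is

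n = [z(0.975)·√(2p̄(1−p̄)) + z(0.80)·√(p₁(1−p₁)+p₂(1−p₂))]² / (p₁−p₂)².

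With an assumed p₁ = 0.58 and p₂ = 0.7 × 0.58 = 0.406, it gives 129, close to 128. The document states no CCI difference or SD. Below, 128 serves only as a sample size.

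**2. Shape of CCI.** From Table 1, CCI = √(sum of weights)/2. No complication gives 0. One grade I complication gives √300/2 = 8.7, and one grade II gives √1750/2 = 20.9. Nothing can fall between 0 and 8.7, and death is set at 100.

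**3. What the pre-test does.** CCI was simulated from the Table 1 weights, with 128 per arm and 1,500 runs per scenario. These inputs are assumptions:
- a Poisson number of complications per patient;
- grades I, II, IIIa, IIIb, IVa and IVb in proportions 30, 40, 15, 6, 6 and 3%;
- 2% deaths.

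| Mean complications, control vs treated | Shapiro-Wilk rejects | t-test significant | Mann-Whitney significant | Two-stage rule |
|---|---|---|---|---|
| 1.0 vs 1.0 | 100% | 4.1% | 5.3% | 5.3% |
| 1.5 vs 1.5 | 100% | 5.8% | 5.3% | 5.3% |
| 1.0 vs 0.7 | 100% | 42% | 59% | 59% |
| 1.5 vs 1.05 | 100% | 56% | 71% | 71% |

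The two-stage rule is the same as Mann-Whitney throughout. Its type I error is nominal within simulation error, √(0.05 × 0.95/1500) ≈ 0.6 points. Under these assumptions it has more power than the t-test.

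**4. What the medians show.** In the 1.0 vs 0.7 scenario the average means were 18.3 and 14.1, a difference of 4.2. The average medians were 16.7 and 5.5, a difference of 11.2. In the 1.5 vs 1.05 scenario the means differed by 24.2 − 18.9 = 5.3 and the medians by 22.8 − 18.3 = 4.5. The gap between medians does not track the mean difference. In a separate set of four assumed scenarios, each with a true benefit (600 runs each), the two medians were identical in 9 to 33% of trials.

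**5. Gain from adjustment.** The document gives no R² (the share of CCI variance explained by covariates), so a range is shown. The standardised difference that gives 80% power at 128 per arm is (1.960 + 0.842) × √(2/128) = 2.802 × 0.125 = 0.350. Adjusted power is Φ(0.350 × √(128/2)/√(1−R²) − 1.960) = Φ(2.802/√(1−R²) − 1.960), and the n per arm needed for 80% power is 128 × (1−R²).

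| R² (assumed) | Power at 128 per arm | n per arm for 80% |
|---|---|---|
| 0 | 80% | 128 |
| 0.05 | 82% | 122 |
| 0.10 | 84% | 116 |
| 0.20 | 88% | 103 |

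This is a t-test approximation. A rank-based simulation gave a gain of roughly 0 to 7 points.

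**6. Centre.** Take 300 patients over seven equal centres, about 43 each. With one central list in blocks of six, the chance that the arms differ by 10 or more patients in at least one centre is about 52 to 55% by simulation. If blocks run within centre, which the article neither states nor excludes, the difference is at most 3 per centre.

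**The case against.** The strongest reply is that an unadjusted rank test is a valid primary analysis in a randomised trial, and that a condensed article commonly leaves covariate adjustment to an analysis plan, which is not shown here. That stands, so the absence of covariates alone would be a weak point. But the article does state a test, a rule for choosing it and a way of presenting CCI. Those choices can be judged as written.

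Several stronger readings are tempting and are not supported:

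- **That the pre-test wastes power or inflates type I error.** Step 3 shows neither. For the same reason, the data-dependent switch between a mean and a rank question has little practical force: one branch is practically always taken.
- **That no usable effect estimate is possible.** The t-test branch yields a mean difference, a 95% interval is mentioned, and a rank-based estimate can accompany Mann-Whitney. The estimate is unspecified, not impossible.
- **That omitting centre undermines the test.** No stated stratification factor is being ignored, and chance imbalance does not bias the test. In simulation with 240 patients in central blocks, unadjusted Mann-Whitney type I error was 5.1% and 4.9% when centre explained 5% and 15% of the variance.
- **That all the covariates are already recorded.** The article says only that relevant factors go on the eCRF, and it offers the subgroups as examples. It does not say whether approach means planned or performed, or whether diagnosis is preoperative or final. Texture is seen during surgery, after the study drug is given.

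Proportional-odds regression also brings an assumption of its own, and other adjusted methods would serve.

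**Conclusion.** The point holds in a limited form. The normality pre-test for CCI serves no purpose, because it will practically always select Mann-Whitney. In that branch the article promises per-arm medians only, and its two analysis sections disagree on range versus interquartile range. No between-arm effect measure is specified for the primary endpoint. Centre and the preoperative factors named for subgroups are unused.

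The consequence is a primary result without a stated effect size, and some lost precision. On the t-test approximation the loss is about 2, 4 or 8 points of power at R² of 0.05, 0.10 or 0.20, and close to nothing if the covariates are weakly prognostic. These figures rest on an assumed R², and on a standardised difference back-solved from a sample size derived for a binary outcome. The claim about the pre-test rests on the form of Table 1 and on assumed complication counts, and it was the same in every scenario tried. The change is worth making because it costs little; the planned test is not invalid.

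**What to change.** Before unblinding, and without sight of outcomes by arm:

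- Drop the normality pre-test for CCI and name one primary analysis. A suitable choice is proportional-odds regression of CCI on treatment, adjusted for centre and for those preoperative factors confirmed to be recorded (for example diabetes, preoperative diagnosis group and planned approach). Report the odds ratio with its 95% confidence interval.
- Add, as support, the adjusted mean CCI difference with a robust 95% confidence interval.
- As a minimum version, use a van Elteren test stratified by centre together with a stated effect measure.
- Keep pancreatic texture to a sensitivity analysis.
- Reconcile range with interquartile range between the two analysis sections.

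The cost is wording, a check of which factors the eCRF holds, slightly more analysis work and a proportional-odds assumption to examine. The sample size need not change for this.

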#### Interim analysis

Planned interim analyses will be performed by the DSMC at recruitment of 150 patients. Any recommendation to proceed with the trial or to abandon for either safety or futility reasons will be communicated with the principal investigators in the first instance. The DSMC is the final arbitrator as to the necessity for safety reporting to the regulatory authorities and/or individual sites.

#### Subgroup analysis

Exploratory post-hoc subgroup analyses are considered to further explore the effects of dexamethasone on postoperative complications. For example, subgroup analyses can be stratified as follows:Robotic pancreaticoduodenectomy vs. open pancreaticoduodenectomyPatients with pancreatic duct adenocarcinoma vs. with other diseasesSoft pancreatic texture vs. hard pancreatic texturePreoperative diabetes vs. no diabetes

## Discussion

With the development of surgical techniques, the high incidences of postoperative complications after PD become the greatest challenge for pancreatic surgeons [26, 27]. To date, few trials have reported satisfactory results. So, there is an urgent need to find effective management to reduce the morbidities after PD.

A single low-dose dexamethasone before the operation is a simple treatment for anesthetists but could make real changes in the postoperative course of PD patients. The anti-inflammatory effect of dexamethasone would mitigate PPAP and reduce the incidence of postoperative complications after PD. The PANDEX trial will test this hypothesis in a high-volume pancreatic center. The results might provide us with a potentially effective therapy for the routine practice of pancreatic surgery and alleviate the burden of postoperative complications in PD patients.

